### Intervention

The program consists of the residents playing Wii bowling in a group with up to three other residents for a period of 6 weeks, for up to 1 hour per session. Wii bowling has been selected as research shows that with older populations it is most popular Wii game and the easiest to learn [17] over the relatively short trial period. It is expected that residents will be able to easily master the game play to allow for social interaction to occur between residents.

Each group requires a minimum of two residents to run each week. The Wii will be located in a quiet area of the facility, and residents will play seated in a semi-circle to reduce the risk of falls. The participants will also be involved in an onsite training session run by the researcher before the commencement of the intervention. Residents will be advised that the purpose of the intervention is to learn a fun, new activity with others.

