### Administration of assessments

A researcher will attend each aged care facility that agrees to participate. A presentation will be given to outline the research, and what it would involve for the residents. One week later, a researcher will approach interested residents on site. Residents will be assessed on their levels of depression, social support, sense of belonging, and self-reported mood at pre-intervention (week 0), post-intervention (week 6), and 2-month follow up (week 14).

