### Statistical analysis

To establish if there are any significant differences between the intervention and the control group on levels of dementia (SLUMS exam), residents' age [30], and length of time in care [31], between groups *t*-tests will be conducted. A series of chi-square tests will be conducted to establish if there are differences between groups and the demographic variables of relationship status, level of education, self-rated health status, and gender. The intervention and control groups will be compared in relation to pre, post, and follow-up changes in depression, sense of belonging, social support, and mood using a mixed model between groups multivariate analysis of variance conducted using SPSS v20.

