### Sample Size and power calculations

GPower [32] analysis indicates that to detect medium effect size with four outcome variables (*f* (V) test = .25) with power of at least .80 and an alpha level of .05, a sample size of 79 participants per condition is sufficient, assuming that these participants complete all questionnaires and complete the intervention program. As his study aims to assess the feasibility of playing Wii bowling in residential age care, a total sample size of 158 may not be able to be obtained. If this occurs, the current study will be marked as a pilot study.

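### The Wii arm is delivered in small play groups, but the planned MANOVA and the 79 per condition treat residents as independent; if group-mates' outcomes correlate, precision and power are overstated

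*Protocol article*

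**What the plan says.** All references are to the protocol article.

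- **Intervention:** the programme is "residents playing Wii bowling in a group with up to three other residents for a period of 6 weeks", and a group needs at least two residents to run. The Abstract gives two sessions a week.
- **Control group:** no Wii activity in the first 6 weeks. After week 6 both arms receive a console.
- **Secondary outcomes and Hypotheses:** interaction between group members is observed at weeks 1, 3 and 6, and positive interaction within groups is expected to rise. The researcher logs attendance, playing time and scores at each session.
- **Statistical analysis:** the arms are compared on depression, belonging, social support and mood "using a mixed model between groups multivariate analysis of variance conducted using SPSS v20". Mixed here means between-within; no random effect for play group or facility is named.
- **Sample size and power calculations:** the aim is "to detect medium effect size with four outcome variables" with "power of at least .80 and an alpha level of .05", and "a sample size of 79 participants per condition is sufficient, assuming that these participants complete all questionnaires and complete the intervention program". No ICC, design effect or number of groups appears.
- **Discussion:** differences between facilities in services or demographics are to be controlled statistically. That does not cover correlation among residents who play together.

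**The concern.** The design is partially nested: residents in one arm are grouped by the delivery of treatment and residents in the other are not. The four primary outcomes, belonging and social support above all, are ones on which people who share sessions could well move together, and the protocol's rationale is that they should. An analysis that counts each Wii resident as an independent observation then understates the variance of the Wii-arm mean. Confidence intervals are too narrow, the nominal .05 level is exceeded, and the planned sample gives less power than stated.

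This source of correlation is separate from the facility. At the planned size there would be roughly 79 / 4 ≈ 20 play groups or more, enough to estimate a play-group variance. Two facilities per arm give almost no basis for estimating a facility variance.

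**Working it through.** **Inputs from the protocol.** Alpha .05; power .80; f(V) = .25, so f² = .0625; 79 per condition, 158 in total; three assessments (weeks 0, 6 and 14); group size m from 2 to 4; complete data assumed.

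**Assumed.** Play-group ICC ρ = .05, .10, .20 (none is stated); all groups the same size; stable membership.

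**Step 1: reproduce the stated figure.** Noncentral F for a group-by-time effect with 2 groups and 3 occasions: df1 = 2, df2 = N − 3, λ = N·f². At N = 158, λ = 158 × .0625 = 9.875, df2 = 155, and power = .802. At N = 157 power is .799. So 158 is exactly the answer when residents are independent, and no clustering allowance is hidden in it. (This is the number for three occasions of one outcome. How it relates to four outcome variables is a separate matter.)

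**Step 2: variance inflation.** The Wii-arm variance is multiplied by DE = 1 + (m − 1)ρ and the control arm by 1. With equal arms, the variance of the difference is multiplied by v = (DE + 1)/2 and the standard error by √v. For m = 4, ρ = .10: DE = 1 + 3 × .10 = 1.30, v = 1.15, √v = 1.07.

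**Step 3: consequences.**
- Power at 158: replace λ by 9.875 / v.
- Type I error, two-arm contrast: 2 × [1 − Φ(1.96/√v)].
- Type I error, 2-df test: P(F(2,155) > Fcrit/v), where Fcrit = 3.054 is the nominal 5% critical value.
- Total N needed: smallest N with power of at least .80 when λ = N × .0625 / v.

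| m | ρ | DE | v | SE ratio | Power at 158 | Type I, contrast | Type I, 2-df | Total N for .80 |
|---|---|---|---|---|---|---|---|---|
| 4 | .05 | 1.15 | 1.075 | 1.04 | .77 | .059 | .061 | 169 |
| 4 | .10 | 1.30 | 1.15 | 1.07 | .74 | .068 | .073 | 181 |
| 4 | .20 | 1.60 | 1.30 | 1.14 | .69 (.685) | .086 | .099 | 204 |
| 2 | .05 | 1.05 | 1.025 | 1.01 | .79 | .053 | .054 | 162 |
| 2 | .20 | 1.20 | 1.10 | 1.05 | .76 | .062 | .065 | 173 |

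For the 2-df test, ρ refers to the changes over time that the test uses.

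**Step 4: what a play-group term leaves unsolved.** With 158 / 4 = 39.5 residents per facility, the facility design effect is 1 + 38.5 × .01 = 1.39 at a facility ICC of .01 and 1 + 38.5 × .05 = 2.93 at .05. The second compares with v = 1.075 for play groups of four at the same ICC. A null simulation used two facilities per arm, 40 residents each, groups of four and a play-group ICC of .05. It compared Wii group means with individual controls, as a stand-in for the mixed model.

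| Facility ICC | Type I error, ignoring play groups | Type I error, allowing for play groups |
|---|---|---|
| 0 | about .06 | .05 |
| .01 | about .10 | about .09 |
| .02 | about .15 | about .13 |
| .05 | about .26 | about .24 |

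The level returns to .05 only when the facility ICC is zero.

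**The case against.** Most of the case on the other side concerns how much can be claimed.

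- **The harm is conditional.** A reader might infer that the standard errors are certainly too small. The protocol does not support that: it gives no ICC, and the bias arises only if the play-group ICC is positive. The stated mechanism makes a positive value plausible but does not establish its size. At .05 with groups of two the standard error changes by about 1%.
- **Stable groups are assumed.** The protocol sets a maximum and a minimum group size but does not say that the same residents play together throughout. Rotation would probably weaken the correlation, and one group ID would then misdescribe the data. The attendance log is not said to record who played with whom.
- **The number of groups is assumed.** About 20 groups requires 79 Wii residents, and the protocol allows that 158 may not be reached. With fewer groups the variance component is poorly estimated.
- **Week 14 differs.** After free play in both arms, treating controls as ungrouped may no longer hold.
- **The facility problem is larger.** A reader might infer that a play-group term puts the clustering right. It does not, as Step 4 shows.

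All five stand as limits. None removes the point, because the stated model and stated sample size both rest on independence within a treatment delivered in groups. The remedy is also different from any remedy for facilities, so the point is worth making separately.

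**Conclusion.** The point holds in conditional form. The sample size is demonstrably an independent-residents figure, and the named analysis has no term for the groups in which the Wii arm is treated. For an assumed ICC of .05 to .20 and full groups of four, nominal standard errors are 3.6% to 12.3% too small (1 − 1/√v), and power is .77 to .69 instead of .80. The type I error is .059 to .086 for a two-arm contrast, or .061 to .099 for the 2-df time-by-group test. With groups of two, the standard error ratio is 1.01 to 1.05 and power is .79 to .76. These figures rest on the assumed ICC, equal group sizes, stable membership and no facility effect. The change should be made, but it is a modest correction and does not make the trial's inference sound while facility clustering is unaddressed.

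**What to change.** 1. Record the play-group composition of each session alongside the attendance already logged, and give each Wii resident an initial play-group ID.
2. At week 6, analyse each outcome with a partially nested linear mixed model: random play-group effect in the Wii arm only, controls as singletons, arm-specific residual variance. Use the same model at week 14 as a sensitivity analysis, since both arms will have had free play by then.
3. If membership rotates, use multiple-membership weights or report the rotation as a limitation.
4. Restate power with DE = 1 + (m − 1)ρ on the Wii arm, over a stated range of ICC and of group size from 2 to 4.
5. State explicitly that this handles play-group correlation only, and that clustering by facility, with two facilities per arm, is the larger source of error and is addressed separately.
6. State that if recruitment falls short the play-group variance will be poorly estimated.

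The cost is one extra item in the session log, revised analysis wording, slightly wider intervals and a lower stated power.

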### Control group

The control group participants will be located in two different aged care facilities. The control group will not take part in any activities involving the Wii console in the first 6 weeks. The control and intervention group will be provided with a Wii console and staff training on how to play Wii bowling at the end of the 6 week intervention period.

### Administration of assessments

A researcher will attend each aged care facility that agrees to participate. A presentation will be given to outline the research, and what it would involve for the residents. One week later, a researcher will approach interested residents on site. Residents will be assessed on their levels of depression, social support, sense of belonging, and self-reported mood at pre-intervention (week 0), post-intervention (week 6), and 2-month follow up (week 14).

### Primary outcomes

The primary outcomes to be assessed are reduction in depressive symptoms and improvements in self-reported mood, sense of belonging, and levels of social support.

#### Depression

The Geriatric Depression Scale Short Form [24] will be used to measure depression. The scale utilises a simple *yes/no* format for ease of administration and consists of 15 items (e.g., Do you often feel helpless?). Higher scores indicate higher levels of depressive symptomatology in an individual. A cut off score of 7 or more will be used for this research with α = .91 [25]. The shorter version of the scale is able to differentiate depression from non-depressed older adults, and has a significant correlation with the original 30 item scale (*r* = .84, *p <* .001, [26]).

#### Social support

Social support will be measured using the Social Provisions Scale [27]. The participants will indicate on a 4-point scale the extent to which each statement describes their current level of social support (e.g., There are people who enjoy the same social activities I do). Responses range from strongly disagree to strongly agree. Cutrona and Russell [27] report coefficient alphas ranging between .65 to .70 and test-retest reliability coefficients ranging from .37 to .66 over a 2 week period.

#### Sense of belonging

To measure sense of belonging, a visual analogue scale will be utilised. The Sense of Belonging Visual Analogue Scale was developed to enable the 18-item Sense of Belonging Instrument [28] to be reduced to a two item visual analogue scale for ease of use. The Sense of Belonging Visual Analogue Scale measures the two theoretical concepts underlying the Sense of Belonging Instrument, these concepts are how much someone feels valued, and their fit with the surrounding environment. The Sense of Belonging Visual Analogue Scale presents participants with two 10 cm lines. At each end of the line opposing statements are placed asking residents about feeling valued and feeling as though they fit in. Respondents will be asked to place a vertical line indicating the extent to which they endorsed the concepts on either extreme. The placement of the line will be measured in centimetres, and rounded to the closest centimetre. Higher scores indicate greater levels of each concept.

The validity of the scale has been established by Morris [29], scores have been correlated with scores obtained on the psychological state sub-scale of the Sense of Belonging Instrument [28]. There was a significant, strong positive correlation between the two instruments (*rho* = .67, *p* < .001).

#### Mood

To measure participant's current mood at the time of completing the questionnaire packages, participants will be asked to indicate “How is your mood right now?” on a visual analogue scale. The scale will be in the same format and scored in the same manner as the sense of belonging visual analogue scale. The residents will be presented with opposing statements at each end of a 10 cm line. The extreme positions will have the statements “worst mood” and “best mood”. Higher scores indicate a better mood. Currently, there is no validity for data for the mood scale (Fig. 2, Instruments used for data collection, Fig. 3, Visual analogue scales).

**Fig. 2 Fig2:**
[figure not shown]
Instruments used for data collection

**Fig. 3 Fig3:**
[figure not shown]
Visual analogue scales

### Secondary outcomes

Participants in the intervention group playing Wii with others will also be involved in a qualitative interval interaction analysis. Onsite observational data will be collected during video game playing sessions in week 1, 3, and 6. Verbatim written transcripts will be made of these sessions. The observational data collected will focus on the interaction between group members to ascertain the type of social interactions that occurs, and if there is an increase over the course of the intervention period. Interaction data will be coded by the key researcher and then analysed utilising Nvivo 10. A researcher will be on site during each session to address any technical issues, but will not participate or interact with group members. Length of time spent playing, high scores, and attendance will be recorded by the researcher for each session. This data will be analysed to establish any differences between the two intervention facilities in game play time, and also to establish how long each resident is playing the game. Game play will be defined as when the resident is actively playing, or watching others play the game.

Post-intervention evaluation will also be conducted using a short answer questionnaire designed specifically for this research to enable participants to provide information about their experience of the intervention. This questionnaire will ask residents questions such as “What did you enjoy about playing the Wii”, “What didn’t you enjoy about playing the Wii”, “Would you prefer to play alone or with other people?” and “Would you continue to play the Wii in the future if it was available?”. These questions were chosen by the researcher to encourage the residents to express any positive or negative aspects of playing the game, as well as any limitations or difficulties they experienced. Staff opinions on the feasibility, ease of use, and enjoyment of the Wii console will also be obtained at the end of the 6 week intervention. Staff opinions will be obtained through semi-structured interviews following a similar format to the post-intervention evaluation questionnaire. This is to establish the staff response to the game play. To establish if residents are able to play Wii bowling without significant staff intervention in the activity, both groups (control and Wii) will be provided with the Wii console, games, and training on how to play at the end of week 6.

### Hypotheses

It is hypothesised that participants in the active Wii condition will demonstrate greater improvements in mood, depression, social support, and sense of belonging, in comparison to those in the control condition. Those in the active Wii condition are hypothesised to also maintain their improvements at the 2 month follow-up. In addition, it is hypothesised that those participants in the active Wii intervention will demonstrate higher levels of within group, positive group interactions from pre to post-intervention.

### Statistical analysis

To establish if there are any significant differences between the intervention and the control group on levels of dementia (SLUMS exam), residents' age [30], and length of time in care [31], between groups *t*-tests will be conducted. A series of chi-square tests will be conducted to establish if there are differences between groups and the demographic variables of relationship status, level of education, self-rated health status, and gender. The intervention and control groups will be compared in relation to pre, post, and follow-up changes in depression, sense of belonging, social support, and mood using a mixed model between groups multivariate analysis of variance conducted using SPSS v20.

### Sample Size and power calculations

GPower [32] analysis indicates that to detect medium effect size with four outcome variables (*f* (V) test = .25) with power of at least .80 and an alpha level of .05, a sample size of 79 participants per condition is sufficient, assuming that these participants complete all questionnaires and complete the intervention program. As his study aims to assess the feasibility of playing Wii bowling in residential age care, a total sample size of 158 may not be able to be obtained. If this occurs, the current study will be marked as a pilot study.

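### The stated 158 residents (79 per condition) do not give .80 power for four outcomes at f(V) = .25: power is about .69 for one four-outcome comparison and about .55 for the group-by-time test

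*Protocol article*

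**What the plan says.** In the protocol article, Sample Size and power calculations sets the target "to detect medium effect size with four outcome variables", with f(V) = .25 and "with power of at least .80 and an alpha level of .05". It concludes that "a sample size of 79 participants per condition is sufficient". A condition is attached, namely no loss of data or of adherence: "assuming that these participants complete all questionnaires and complete the intervention program". The section then warns that "a total sample size of 158 may not be able to be obtained" and says that in that case the study will be labelled a pilot.

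Statistical analysis describes the test to be powered. The method is named at the end of that section: "using a mixed model between groups multivariate analysis of variance conducted using SPSS v20". What it is applied to is stated just before, where the two groups are to be "compared in relation to pre, post, and follow-up changes in depression, sense of belonging, social support, and mood". Study design fixes three assessments, at weeks 0, 6 and 14. Primary outcomes lists the same four constructs. The GPower procedure, the number of groups and the number of measurements entered are not given.

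**The concern.** The inputs that are stated (four outcome variables, f(V), alpha, target power) together with the two conditions are enough to check the figure for a single four-outcome comparison. The answer given looked too small for a test that spends four or more numerator degrees of freedom.

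Two things are at stake. First, the article credits its main multivariate test with power that it lacks, even with complete data. Second, 158 is the article's own line between a pilot and a full study. If 158 completers were reached, the study would carry the full-study label while its main test stood well below .80 at the stated effect.

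**Working it through.** **Inputs**
- Two conditions: Study aims and Study design.
- Four outcomes, f(V) = .25 (so f² = .0625), alpha .05, power at least .80, 79 per condition, N = 158, no loss: Sample Size and power calculations.
- Three occasions: Study design.

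**Formula.** With two groups, Pillai's V has an exact F test. Let p be the number of response dimensions tested.
- df1 = p
- df2 = N − 2 − p + 1
- Power = P(F′ > critical F at .05), where F′ is noncentral F with df1, df2 and noncentrality λ.
- Two conventions for λ are in use: (a) λ = f²·N and (b) λ = f²·df2. Both are shown.

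**Can the stated figure be reproduced?** Yes, but with p = 2. At N = 158, df2 = 158 − 2 − 2 + 1 = 155.
- (a) λ = .0625 × 158 = 9.875, power .802. At N = 157 power is .7995, so 158 is the exact minimum.
- (b) λ = .0625 × 155 = 9.69, power .794, and the minimum is 161.

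**The stated inputs: four outcomes, one group comparison (p = 4).** df2 = 158 − 2 − 4 + 1 = 153.
- (a) λ = 9.875, power .694.
- (b) λ = .0625 × 153 = 9.56, power .678.

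**The group-by-time effect in the analysis section: four outcomes, three occasions (p = 4 × (3 − 1) = 8).** df2 = 158 − 2 − 8 + 1 = 149.
- (a) λ = 9.875, power .555 (.5547).
- (b) λ = .0625 × 149 = 9.31, power .525.

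| Test, two groups, f(V) = .25 | df1 | N for .80, (a) / (b) | Power at 158, (a) / (b) | f(V) detectable with .80 at 158, (a) |
|---|---|---|---|---|
| Numerator df 2 | 2 | 158 / 161 | .80 / .79 | .25 |
| Four outcomes, one comparison | 4 | 196 / 201 | .69 / .68 | .28 |
| Four outcomes, group by time | 8 | 249 / 257 | .55 / .53 | .32 |

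On convention (a), the shortfall in residents is 196 − 158 = 38 for df 4 and 249 − 158 = 91 for df 8. In equal groups that convention means 98 per condition, or 125 after rounding 249 up to 250.

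**Other readings tried**
- Reading .25 as f² or as V gives totals of only 41 to 77 for df 4 or 8, under either convention.
- Entering 4 as the number of repeated measurements (df 3) needs 179 to 183.
- Four outcomes with three or four groups give 97 to 129.
- A one-way ANOVA with three groups at f = .25 also gives 158, but this trial has two conditions.

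None of the two-group, four-outcome settings tried returns 158.

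**The case against.** **The settings are not reported.** A journal article commonly leaves software settings to the full protocol, so one cannot say how 158 arose. This stands as far as the origin goes. A reader might infer that the calculation was run for a single outcome over three visits, because that setting returns 158 exactly. Two response variables at one time, or three groups on one outcome, return it too, so the documents do not establish which was used. The shortfall does not depend on the explanation.

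**The .55 figure depends on a reading.** The sample size section says only that there are four outcomes, and the analysis section does not name the decisive multivariate effect. This also stands. The failure on the article's own stated inputs is .69 against .80. The .55 applies if the group-by-time test is the powered one, which the wording about changes over three assessments makes plausible but does not settle. In addition, a fixed f(V) is not the same underlying effect when dimensions are added, so the rows of the table are different alternatives and not one effect tested three ways.

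**Belonging could count as two outcomes.** The scale has two lines, and the article says "Higher scores indicate greater levels of each concept", so a reader might push the degrees of freedom higher still. The outcome list, the analysis section and the sample size section all count belonging as one of four outcomes, and nothing says that the items will be analysed separately. That extension is not supported.

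**The article already hedges.** It makes the figure conditional on full completion and provides for pilot status if recruitment falls short. That limits how a null result would be read below 158. It does not repair the power claim, because the same 158 is the threshold. A reader might conclude that a null result is bound to be over-interpreted. The documents do not show that, and the risk arises only if 158 completers are reached.

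**Conclusion.** The concern holds as an arithmetic error. On the article's own inputs (two groups, four outcomes, f(V) = .25, alpha .05), 158 completers give power of about .69 (.68 under the other convention), and .80 needs 196 to 201. If the powered effect is the 8-df group-by-time test, power is about .55 (.53), and .80 needs 249 to 257. The result rests on the noncentral F distribution for Pillai's V with complete data, independent residents and f(V) held at .25. Any dropout would lower power further. The choice of noncentrality convention moves power by two to three points and does not change the conclusion. How 158 was obtained remains an inference.

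**What to change.** Keep the sample size and restate the power in Sample Size and power calculations:
- At f(V) = .25, 158 completers give about .69 power for four outcomes in a single comparison, with .80 reached at f(V) of about .28.
- At f(V) = .25, they give about .55 power for the 8-df group-by-time MANOVA, with .80 reached at f(V) of about .32.
- State which of these effects is the powered one, and report the GPower procedure and settings.
- Do not treat reaching 158 as showing .80 power when deciding whether the study is a pilot.

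The correction should not be made by tying the .80 to one named outcome. That would change the four stated primary outcomes, and Study design says that recruitment ran until November 2014.

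The cost is a short rewording and a less favourable stated power. No added enrolment is needed.

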### Participants

Participants will be recruited from their place of residence with the approval of the aged care facility manager. Four aged care facilities will be sought for participation. Exclusion criteria are: severe cognitive impairment or dementia as assessed by the Saint Louis Mental Status Examination (SLUMS, [23, 24]), diagnosis of bipolar affective disorder, schizophrenia, intellectual disability, severe hearing impairment, acute illness, inability to communicate in English due to non-English speaking background, age of less than 65 years, epilepsy or seizures, pacemaker or implanted medical device or physical disability preventing use of the Wii console. For this research, participants will be excluded if they received a score of 20 or less on the SLUMS exam indicating the presence of dementia or severe cognitive impairment [24]. These exclusion criteria are based on previous research and on the safety precautions provided in the instruction manual from the Wii. Written consent will be gained from both the participants and from the aged care facility manager.

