A second potential limitation is that the intervention will be compared to a control group in a separate aged care facilities. This is necessary to ensure adequate numbers in each group. Residents in the second aged care facility may have access to different services or activities already integrated into the aged care facility. Also, residents across the facilities may vary significantly on demographic variables. To minimise the potential impact of this aged care facilities from similar socio-economic areas will be selected and any differences will be statistically controlled for in the analyses.

The study is also limited by the use of self-report measures with older adults. Factors, such as acute illness, changes in physical functioning, or cognitive impairment can influence the accuracy of self-report measures in hospitalised older adults [34]. A number of residents may exhibit low level cognitive impairment as assessed by the SLUMS exam. These residents may have trouble comprehending some of the questions, resulting in inaccurate results on the self-report measure of depression, social support, and sense of belonging.

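### The stated power of .80 at 79 residents per condition holds only if residents within a facility are uncorrelated, although allocation is by facility with two facilities per arm

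*Protocol article*

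**What the plan says.** The section on sample size and power reports a G*Power calculation "to detect medium effect size with four outcome variables", with f(V) = .25. It concludes that "with power of at least .80 and an alpha level of .05, a sample size of 79 participants per condition is sufficient". The only condition attached is that these participants complete the questionnaires and the program. The section then allows that a total of 158 may not be reached, and adds: "If this occurs, the current study will be marked as a pilot study".

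The design is described elsewhere in the article. The abstract allocates participants by where they live. Under Participants, "Four aged care facilities will be sought for participation". The Control group section places the controls in two facilities, and the Secondary outcomes section refers to two intervention facilities. The Statistical analysis section compares the groups with a multivariate analysis of variance on residents and names no facility term. As a limitation, the Discussion notes that "the intervention will be compared to a control group in a separate aged care facilities". It answers this by choosing facilities from similar socio-economic areas and by statistical control of differences.

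**The concern.** A calculation that counts 158 residents as 158 independent observations does not match a design in which whole facilities go to one arm. Residents of one facility share staff, activities and surroundings, and intervention residents also play together in small groups. If their changes over time are positively correlated, the arm difference is estimated less precisely than 158 independent residents would allow, and the stated power is too high.

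The article uses the stated power to support its effectiveness aim, and uses 158 as the number below which the study is relabelled a pilot. A reader of a completed study with 158 residents would take it to have the stated power. A null result could then be given more weight than it deserves.

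**Working it through.** **Inputs from the protocol article.** Alpha .05, target power .80, f(V) = .25, 79 per condition (158 in total), three occasions (weeks 0, 6 and 14), two groups, four facilities with two per arm.

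**Inputs assumed.** Facility sizes are not stated, so four equal facilities are assumed: m = 158 / 4 = 39.5. No ICC is stated, so a range of .005 to .05 is used. The relevant ICC is that of the change being tested, which may be smaller than that of raw scores.

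**Step 1: reproduce the stated figure.** For a repeated-measures multivariate test of group by time, with two groups and three occasions, the degrees of freedom are 2 and N − 3, and the noncentrality is λ = f(V)² × N.
- At N = 158: λ = .0625 × 158 = 9.875, power .802.
- At N = 157: λ = .0625 × 157 = 9.8125, power .799.

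The smallest N reaching .80 on this test is therefore 158, and the slack is one resident. That this is the test behind the figure is inferred from the match. The article speaks of four outcome variables, and a two-group test on four outcomes (4 and N − 5 df) with the same f(V) would need 196 residents; its power at 158 is .69. The steps below use the version that matches 158, which is the more favourable of the two.

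**Step 2: allow for facilities.** Design effect DE = 1 + (m − 1) × ICC = 1 + 38.5 × ICC. Effective sample size N_eff = 158 / DE. Power comes from the same test with N_eff in place of N.

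| Assumed ICC | DE | N_eff | λ = .0625 × N_eff | Power |
|---|---|---|---|---|
| 0 | 1.00 | 158 | 9.88 | .80 |
| .005 | 1.19 | 132 | 8.28 | .72 |
| .01 | 1.39 | 114 | 7.13 | .65 |
| .02 | 1.77 | 89 | 5.58 | .54 |
| .05 | 2.93 | 54 | 3.38 | .34 |

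**Step 3: find where .80 is lost.** At an ICC of .0001, DE = 1.00385, N_eff = 157.4 and power is still just above .80. At .0002, DE = 1.0077, N_eff = 156.8 and power is .799. The stated power therefore survives only a correlation that is practically zero.

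**Step 4: degrees of freedom.** The design effect lowers the effective sample size but leaves the denominator degrees of freedom at resident level. If inference were made at facility level, four facilities less two arms would leave 2 denominator degrees of freedom, and power would be lower than in the table. These are not the 2 numerator degrees of freedom of Step 1, which come from the three occasions.

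**The case against.** **The arithmetic is not wrong.** This is correct. Under independence 158 is reproduced, and the fault lies in the unstated assumption.

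**The ICC is unknown and could be very small.** This also stands as a limit on the size of the effect. At an ICC of .001 power is still .79. The table is a sensitivity range, not an estimate, and 39.5 per facility is simply 158 divided by four. But no value is offered to support zero, and the margin is one resident.

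**The article already acknowledges differences between facilities.** It does, and it calls the design quasi-experimental. Choosing similar areas and adjusting for measured differences addresses confounding. It does not restore the effective sample size lost to correlation within facilities.

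**Stronger readings that the documents do not support.**
- A reader might infer that the article declares any study reaching 158 adequately powered. It says only the reverse: falling short makes the study a pilot. That reaching 158 is enough is an implication, and the text should close it off.
- A reader might quote much lower powers, such as .41 even at zero ICC, from a facility-level t test of a standardised difference of 0.5 in one outcome on 2 degrees of freedom. The plan does not propose that test, and f(V) = .25 corresponds to such a difference only if the whole effect lies in a single contrast. Those figures are not used here.
- A reader might conclude that the comparison must be estimation only, whatever number is recruited. That would change the stated aim, hypotheses and analysis. It is a debatable trade-off and does not follow from the error in the power statement.

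**Conclusion.** The point holds: the power statement is wrong as written for this design. Power of at least .80 at 79 per condition requires independent residents, and allocation by facility with two facilities per arm gives no ground for that. On the test that reproduces 158, power falls to about .72, .65, .54 and .34 at assumed ICCs of .005, .01, .02 and .05, and it would be lower still with facility-level inference. The direction is firm for any ICC of change above about .0001. The size depends on the assumed ICC, on equal facilities of 39.5 residents, and on the inferred three-occasion test. Full completion, which the article assumes, is kept throughout.

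**What to change.** In the section on sample size and power:
1. State that .80 at 158 assumes residents within a facility are uncorrelated.
2. Give effective sample size and power for four facilities over an assumed ICC range, for example .005 to .05 as tabulated above, labelled as an assumption.
3. Add that reaching 158 does not by itself make the study adequately powered, so that the pilot caution does not depend on 158 alone.

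The cost is a revised paragraph and a less favourable stated power. No further residents or facilities are needed, and the aim, hypotheses and analysis need not change. Because the article says that recruitment ran until November 2014, a change of wording is also what remains feasible.
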